## Abstract

**Introduction:**

Paediatric fractures are common but can be easily missed on radiography leading to potentially serious implications including long-term pain, disability and missed opportunities for safeguarding in cases of inflicted injury. Artificial intelligence (AI) tools to assist fracture detection in adult patients exist, although their efficacy in children is less well known. This study aims to evaluate whether a commercially available AI tool (certified for paediatric use) improves healthcare professionals (HCPs) detection of fractures, and how this may impact patient care in a retrospective simulated study design.

**Methods and analysis:**

Using a multicentric dataset of 500 paediatric radiographs across four body parts, the diagnostic performance of HCPs will be evaluated across two stages—first without, followed by with the assistance of an AI tool (BoneView, Gleamer) after an interval 4-week washout period. The dataset will contain a mixture of normal and abnormal cases. HCPs will be recruited across radiology, orthopaedics and emergency medicine. We will aim for 40 readers, with ~14 in each subspecialty, half being experienced consultants. For each radiograph HCPs will evaluate presence of a fracture, their confidence level and a suitable simulated management plan. Diagnostic accuracy will be judged against a consensus interpretation by an expert panel of two paediatric radiologists (ground truth). Multilevel logistic modelling techniques will analyse and report diagnostic accuracy outcome measures for fracture detection. Descriptive statistics will evaluate changes in simulated patient management.

**Ethics and dissemination:**

This study was granted approval by National Health Service Health Research Authority and Health and Care Research Wales (REC Reference: 22/PR/0334). IRAS Project ID is 274 278. Funding has been provided by the National Institute for Heath and Care Research (NIHR) (Grant ID: NIHR-301322). Findings from this study will be disseminated through peer-reviewed publications, conferences and non-peer-reviewed media and social media outlets.https://www.isrctn.com/ISRCTN12921105

**Trial registration number:**

ISRCTN12921105.

STRENGTHS AND LIMITATIONS OF THIS STUDYPerforming a large multireader study evaluating paediatric fracture detection with and without artificial intelligence (AI) assistance across different medical subspecialties and experience levels will better evaluate which healthcare professionals benefit most from AI assistance.Our imaging dataset represents a range of children’s ages and body parts across multiple National Health Service trusts to comprehensively evaluate performance of a commercially available AI algorithm.The UK-based population used in this study, lack of patient history with predefined simulated clinical management choices may not exactly mimic real-world practices and outcomes.Replicating societal and ethical biases, with a comprehensive health economic evaluation of providing AI assistance for fracture detection is difficult to achieve, but our study will provide a guide for future studies.

## Introduction

 Approximately, half of all the 12 million children (<16 years) in the UK will fracture a bone during childhood.^1 2^ Radiographic imaging is the first-line imaging tool for assessing the presence and extent of injury. Unfortunately, the interpretation of paediatric fractures is challenging for many healthcare professionals (HCPs) as children sustain different types of injury to adults, which can sometimes be subtle to identify (eg, buckle or Salter Harris fractures), exhibit a wide range of normal appearances across different ages and, sometimes normal physes can be mistaken for injuries. Furthermore, the level of experience of HCPs varies and while patients should, under best practice principles, not be discharged from hospital without a radiology report, in reality, this is not usually available.

In one study, researchers found that misdiagnoses were made in 10% of children’s fractures by emergency doctors.^3^,^6^ Unfortunately, due to workforce pressures and staff shortages,^7^ doctors with subspecialist skills in imaging or musculoskeletal injuries are not readily available 24/7 in a busy emergency department. This leads to potential delays in recognising mistakes,^8^,^13^ long-term pain and discomfort for the child and, in some situations, missed opportunities for safeguarding (as fractures can be the first sign of inflicted injury).^14^

Recently, many artificial intelligence (AI) tools have been developed and demonstrated high diagnostic accuracy rates for the detection of fractures on imaging, in some cases to the same or higher accuracy as a radiologist.^15 16^ Many of these tools, however, have been specifically designed for adults, although encouraging results have been demonstrated when these tools have been applied to children.^17 18^ Within the last year, one AI tool has specifically been approved by the US Food and Drug Administration (FDA) for use in children over the age of 2 years. If implemented clinically, it could potentially improve the quality of paediatric care, streamline orthopedic clinic referrals and reduce the likelihood of medical litigation.^19^

Nonetheless, widespread adoption of AI within the National Health Service (NHS) is still nascent, with various barriers to adoption identified, of which lack of sufficient evidence is one major concern.^20 21^ There is, therefore, a vital and crucial need to evaluate how such a tool may help (or hinder) different members of staff in this clinical care pathway and whether the use of such a tool would make any difference to patient management.

### Objectives

In this study, the aim is to evaluate whether using a commercially available AI tool certified for paediatric use could help HCPs make better decisions about patient care.

Primary objective:

Determine differences in diagnostic accuracy rates of HCPs for paediatric fracture detection, before and after using the AI tool.

Secondary objectives:

Determine whether differences in accuracy rates or effect of adding AI varies according to job role and experience.Determine whether user confidence in fracture diagnosis changes when using the AI tool.Determine whether management plans are altered following the use of the AI tool.

## Methods and analysis

### Study design

The overall study design is of a cross-over multireader multicase (MRMC) study, where each reader (a HCP) will act as their own control across two imaging interpretation stages, with an interval washout period of at least 4 weeks duration (figure 1). Differences in diagnostic accuracy rates between stages, changes in reader’s confidence rates and simulated patient management will be compared. Subgroup analyses will be conducted according to reader specialty area, experience and body part interpreted.

**Figure 1 F1:**
[figure not shown]
A diagrammatic flow chart of the multireader multicase (MRMC) study outline. AI, artificial intelligence.

At the first interpretation stage (1 September 2024–31 October 2024), each reader will review a dataset of 500 paediatric limb radiographs (some normal and some abnormal) without AI assistance, then after the washout period (1 November 2024–30 November 2024), they will proceed with the second interpretation stage (1 December 2024–31 January 2025) where they will each read the same dataset with AI assistance. The order of the radiographs, and thus imaged body parts and those with and without abnormalities, will be randomly ordered within the dataset for every reader at each interpretation stage to further reduce recall bias.

Readers will complete the imaging interpretations online, via a password-protected and secure imaging platform (details below). They will be given a 2-month period to complete the exercise and are informed not to seek help in the imaging interpretation with anyone else. Clinical information associated with each radiograph will include the age of patient and gender. Mechanism of injury, pain location, history will not be provided. The reader will be asked to assume that there is generalised pain at the joint in question, and no significant medical history (ie, no genetic or metabolic bone disorder or known malignancy).

Feedback requested from each reader for each radiograph will include:

Marking the site of a fracture on each image (or selecting ‘no fracture’).Confidence in their decision using a 5-point Likert scale (1=not confident; 5=absolutely certain).Selecting the most likely management for the patient. This will be done by providing each reader with a drop-down menu of seven predefined plans, tailored to each subspecialty, with the option for free-text comment. Examples of the different options are provided in figure 2.

**Figure 2 F2:**
[figure not shown]
Simulated patient management options provided to different subspecialty readers recruited in this study. For every case reviewed, the reader will be asked to select the single best treatment plan. They will be presented with slightly different options depending on their area of medical expertise. ED, emergency department.

### Inclusion and exclusion criteria (imaging cases)

500 anonymised paediatric radiographic examinations (‘cases’) will be derived from a larger 5-year retrospective dataset of appendicular radiographs acquired in children from two NHS trusts (King’s College Hospital NHS Foundation Trust and St George’s University Hospitals NHS Foundation Trust). Both trusts are major trauma centres located in London, UK serving adult and paediatric cases. All radiographic imaging was acquired as part of routine clinical care. No change in patient management will occur as a result of this study, nor was any change in the usual imaging protocol required for this retrospective data collection.

We will include a mixture of normal and abnormal radiographic examinations according to the minimum ratio determined by our sample size calculation below. Four body parts will be used: wrist, elbow, knee and ankle. These were chosen because limbs account for 81.5% of all paediatric injuries,^22^ with those occurring at the knee, wrist and elbow being most commonly missed.^23^ Wrist and elbow fractures encompass 20.5% of all paediatric fractures and missed fractures in these areas are one of the most common reasons for litigation in children’s orthopaedic care.^24^ Although ankle fractures are less common, they account for up to 25% of all growth plate injuries^25^ and thus carry a high potential for long-term growth disorders if misdiagnosed.

Our inclusion criteria for all radiographic imaging in the subset of 500 cases include:

Children aged between 2 and 18 years old (as the intended commercial AI tool is not regulated for children under 2 years of age).

In order to effectively evaluate how well the AI tool could help HCPs identify easily missed fractures, we will include abnormal radiographs that do not contain ‘obvious’ fractures. Obvious fractures will be defined as any fracture that meets at least one of the following criteria and therefore excluded:

Any imaging with a ‘Red Dot’ annotation on the radiograph that cannot be removed (denoting the presence of either a true or false abnormality identified by the radiographer).Any fracture which is angulated by more than 5°.Any fracture which is displaced (>5 mm) or comminuted (multifragmented).Any fracture impacted/shortened by >5 mm.Any fracture with obvious callus formation/sclerosis.

As we will be evaluating the performance of acute fracture detection in an emergency setting, we will exclude healing fractures. Incidental bone lesions will also be excluded from our study, however, normal anatomical variants will be included.

### Study cohort characteristics (imaging cases)

Cohort demographic characteristics for whole population and abnormal dataset for this study are available in online supplemental tables 1–3, with demographic data on normal dataset in online supplemental table 4. Overall, 500 different radiographic examinations across 500 different paediatric patients (none included more than once) will be used (comprising 183 fractures in 181 patients). The dataset will consist of 256 boys (97 with fractures) and 245 girls (84 with fractures), with mean age of 10 years (range 2–17 years).

The most common fractured bone in our dataset is the distal radius (41/181, 22.4% fractures), and the three the most common fracture types are Salter Harris 2 type injury (41/183, 22.4%), buckle fracture (39/183, 21.3%) and transverse fracture (28/183, 15.3%).

We will invite readers from different specialties and experience levels to participate. These will include HCPs working in radiology (including doctors and reporting radiographers), the emergency medicine department (including doctors and senior triage nurses) and orthopaedic surgeons. All experience levels will be welcome to participate, including those with a subspecialty interest within their field (eg, paediatric orthopaedic surgery, paediatric radiology). Readers will, however, be excluded if they do not routinely review paediatric radiographs as part of their expected job role.

Radiologists and reporting radiographers will be recruited voluntarily through society newsletter announcements via the European Society of Paediatric Radiology (ESPR), European Society of Skeletal Radiology (ESSR) and the British Societies of Paediatric Radiology and Skeletal Radiology (BSPR, BSSR) as well as Society of Radiographers (SoR). Emergency medical staff will be recruited through existing local collaborations, via the Royal College of Emergency Medicine (RCEM) and Association of Paediatric Emergency Medicine (APEM). Orthopaedic surgical colleagues will be recruited also via local collaborations, and via the British Society for Children’s Orthopaedic Surgery (BSCOS). All announcements and invitations to participate will be also posted via study collaborators through their personal social media channels.

We anticipate a minimum of 40 readers (approximately 14 readers from each specialty) equally split between trainees and consultant-level experience. Each reader will be provided instructions on how to participate in the study and complete a consent form online asking about their demographic details, job role/specialty and experience level. Prior to any interpretation, a short video and instruction sheet on how to use the online reporting platform will be provided. Reporters will be asked to replicate their usual reporting practices as far as possible (eg, use of a suitable monitor, dim lighting) and would be able to use reference tools (eg, textbooks or websites) that they would normally consult for this task, but just not to consult other reporters.

### Intervention (AI tool)

Our ‘intervention’ will be the use of a commercially available AI tool called ‘BoneView’ (V.2.3.0) produced by a French AI vendor called Gleamer (Paris, France. https://www.gleamer.ai/). The tool received conformity (CE Class 2A EU MDR and FDA) approval for fracture detection in adults and children (aged >2 years old) in March 2022^26^ on full-resolution Digital Imaging and Communications in Medicine (DICOM) images. This product was chosen as it was the first to achieve FDA approval for use in children and had the greatest evidence basis among all commercial products for fracture detection on radiographs.^19^ The full details of how the deep learning algorithm was developed and tested have been described in the existing literature,^17 27 28^ therefore, only a brief overview of how the product was developed is provided here.

The algorithm is a Deep Convolutional Neural Network-based on the object detection framework ‘Detectron 2’ written and further engineered in Pytorch (V.1.3). It was developed based on a data set of 312 602 radiographs from patients across over 60 radiology departments collected from January 2011 to May 2021. 30% of the radiographs included in the dataset were paediatric (<21 years). When the algorithm confidence surpasses that of a predefined threshold set during algorithm development, the AI tool (BoneView) will create an output of a duplicate radiograph in the imaging examination with either a region of interest on the radiograph with a white square box stating presence of a fracture, a region of interest on the radiograph with a dashed white square box stating ‘indeterminate’ fracture or no overlay with a note below the image stating no fracture. The data set of the present study does not overlap with any examinations used in the development dataset used to create the AI tool, and nor with any data in this study be used to further train the commercial AI tool.

There have been at least three prior publications evaluating the performance of this AI tool within a French, American and Swiss paediatric dataset across a similar range of body parts proposed in this protocol.^17 18 29^ Two of these studies have included a smaller dataset than this planned study (n=300)^17 18^ with an equal split of normal and abnormal cases (not reflective of clinical practice). One was a MRMC study design using eight radiologist readers.^18^ None of the prior studies included a simulated patient management plan component, nor a multidisciplinary team of readers as this study is planning to.

Gleamer has provided its AI tool free of charge for evaluation in this trial but has no involvement in the study design, data analysis, reader recruitment or the decision to publish the final results.

### Reference (ground truth) standard

We will use a consensus interpretation by an expert panel of two paediatric radiologists, both with at least 5 years of subspecialist radiology experience as the reference standard (so-called ‘ground truth’) for this dataset. A bounding box around the entire area of bone fracture on each image (if present) will be assigned where the examination is abnormal. Reference radiologists will have access to the radiographic imaging and original imaging report when setting the ground truth bounding box, as well as any follow-up imaging available; none of this will be available to recruited readers. Disagreements will be resolved by a third musculoskeletal radiologist (with similar experience level).

### Data deidentification and secure storage

Scans selected for the study will be deidentified using a software called XNAT V.3.2.4,^30^ an open source research platform for image-based biomedical research, before being uploaded to a secure image viewing platform for reader interpretation. Access to the platform will be controlled via separate user accounts and passwords for each recruited reader.

All study data generated by the readers’ interpretations will be entered into a password-protected and secure database. Individual reader accuracy scores will be anonymised, and the research team will not have access to the identifying link between the participants’ personal details and the data. Data about the readers’ experience level and subspecialty will be retained to allow group comparisons.

All research staff will comply with the requirements of the Data Protection Act 2018^31^ with regard to the collection, storage, processing and disclosure of personal information and will uphold the Act’s core principles. Data will be collected and maintained according to Good Clinical Practice standards.^32^

### Statistical methods/data analysis plan

The STARD-AI (Standards for Reporting of Diagnostic Accuracy - Artificial Intelligence) and CLAIM (Checklist for AI in Medical Imaging) guidelines will be adhered to in the reporting of this study.^33 34^ Diagnostic accuracy of the readers (with and without AI assistance) for each body part will be derived (ie, sensitivity, specificity, positive predictive value and negative predictive value). A true positive result will be counted if a mark made by a reader at the site of a suspected fracture falls within the area of the predefined ‘ground truth bounding box’ area set by the reference radiologists. If the mark made by a reader falls outside a bounding box, it will be counted as a false positive. Where a bounding box was set by the ground truth, but no mark made on the image then a false negative result will be assigned to the reader.

Estimates of these accuracy statistics will be derived through multilevel logistic regression models, with the reader included as a random-intercept. From these models, we will report 95% CIs, and p values (significance level set at 5%). Independent variables will be added, including the reader’s job role and experience, to assess their relationship with diagnostic accuracy. We will additionally present these same statistics to the reader, as derived through the random effects of the models, to explore the relationship between sensitivity and specificity. Intraobserver variability for the diagnostic accuracy of fracture detection before and after the use of AI assistance will also be evaluated, with subanalysis conducted to account for different reader medical specialty subgroups.

We will assess for differences in confidence scores for correctly identified images between HCPs with and without AI guidance, and also whether there were significant differences between readers across specialties and experience levels. We will also evaluate how an indeterminate AI reading affects reader decisions.

Changes in clinical management will be compared using descriptive statistics (ie, frequency and percentages) to determine, for example, how many children would be discharged with a missed fracture, or unnecessary second opinions/additional imaging sought for cases with and without AI assistance. This could provide information to help estimate potential future benefit and cost savings to the NHS at a future clinical implementation stage, where appropriate.

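### The scoring rule never counts a fracture marked only at the wrong site as a miss, so with the usual denominators sensitivity is overstated, specificity is understated, and the AI contrast is distorted in a direction the protocol does not fix

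*Protocol article*

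**What the plan says.** The Study design section asks each reader for "Marking the site of a fracture on each image", or a choice of no fracture. The Statistical methods/data analysis plan section turns these responses into counts by three rules.

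- **True positive:** "A true positive result will be counted if a mark made by a reader at the site of a suspected fracture falls within the area"; the area meant is the ground-truth box.
- **False positive:** "If the mark made by a reader falls outside a bounding box, it will be counted as a false positive". The rule is not restricted to cases without a fracture.
- **False negative:** "Where a bounding box was set by the ground truth, but no mark made on the image then a false negative result" is assigned.

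A true negative is not defined. The measures to be reported are "sensitivity, specificity, positive predictive value and negative predictive value", estimated by multilevel logistic regression with a random intercept for reader. The Reference standard section places boxes only on abnormal examinations. The primary objective is the difference in diagnostic accuracy before and after the AI tool.

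**The concern.** A fractured case marked only at a wrong site meets the false-positive rule. It fails the false-negative rule, because a mark was made. No other sentence makes it a miss. Clinically it is one: the reader did not find the fracture.

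With the usual denominators, each such read leaves TP+FN, although the case is abnormal, and joins TN+FP, although the case is not normal. Whether an abnormal case stays in the sensitivity denominator then depends on what the reader did. Because each reader acts as their own control, the set of fractured cases that counts can differ between the unaided and aided stages for the same reader. The primary comparison would then not be made on a common set of cases.

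A case with one mark inside the box and another outside also yields a true positive and a false positive together, so the counts need not add up to the number of cases.

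**Working it through.** **Inputs from the article.** There are 500 examinations, with 183 fractures in 181 patients (Study cohort characteristics). Abnormal cases are 181 and normal cases 500 - 181 = 319. No figure in the article depends on the scoring rule, so there is none to reproduce.

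**Assumed inputs (not in the article).** c is the share of abnormal cases with a mark inside the box, taken as 0.80. w is the share marked only at a wrong site, taken from 0 to 15%. The unmarked share is 1 - c - w. False calls are made on 10% of normals, so TN = 0.90 × 319 = 287.1.

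**Formulas.**
- Rule as written, usual denominators: sensitivity = c/[c + (1 - c - w)] = c/(1 - w); specificity = TN/(319 + 181w).
- Case-level scoring, wrong-site-only mark counted as a miss: sensitivity = c; specificity = TN/319.

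| w | 181(1 - w) | Sensitivity by rule | 319 + 181w | Specificity by rule |
|---|---|---|---|---|
| 0% | 181.00 | 0.800 | 319.00 | 0.900 |
| 2% | 177.38 | 0.816 | 322.62 | 0.890 |
| 5% | 171.95 | 0.842 | 328.05 | 0.875 |
| 10% | 162.90 | 0.889 | 337.10 | 0.852 |
| 15% | 153.85 | 0.941 | 346.15 | 0.829 |

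Case-level scoring gives 0.800 and 0.900 in every row.

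**Effect on the AI contrast.** With subscripts 1 (unaided) and 2 (aided), the error in the difference is c2·w2/(1 - w2) - c1·w1/(1 - w1). Its sign depends on how w changes. The table uses assumed counts on 181 abnormal cases. The unaided stage has 140 correct, 15 wrong-site and 26 unmarked: 140/166 = 84.3% by the rule and 140/181 = 77.3% by case. Each aided scenario has 155 correct, so the case-level gain is always 15/181 = 8.3 points.

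| Aided: wrong-site / unmarked | Sensitivity by rule | Gain by rule | Case-level gain |
|---|---|---|---|
| 4 / 22 | 155/177 = 87.6% | 3.2 points | 8.3 points |
| 15 / 11 | 155/166 = 93.4% | 9.0 points | 8.3 points |
| 20 / 6 | 155/161 = 96.3% | 11.9 points | 8.3 points |

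The sign can also reverse. If c rises from 0.80 to 0.85 while w falls from 10% to 3%, the rule gives 0.80/0.90 = 0.889 and then 0.85/0.97 = 0.876, a fall despite a real gain of 5 points. If c stays at 0.80 and w falls from 10% to 3%, the rule gives 0.889 and then 0.80/0.97 = 0.825, a fall with no change in detection. In both cases specificity by the rule rises from 287.1/337.10 = 0.852 to 287.1/(319 + 5.43) = 0.885, although behaviour on normal cases has not changed.

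**The case against.** The strongest reply is that the article states neither the denominators nor the outcome variable of the regression models. If sensitivity is modelled on abnormal cases with the outcome correctly marked or not, a wrong-site read scores zero and stays in. If specificity is modelled on normal cases only, marks on abnormal cases never enter it. This stands as a condition on the consequence: the distortion follows under TP/(TP+FN) and TN/(TN+FP). It does not rescue the text. The scoring rules are stated outright, and an analysis plan that handled these reads correctly would have to depart from the false-negative rule as written. This is a stated rule that misclassifies, not a detail left for later.

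A reader might infer several stronger points that the article does not support.

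- **All missed fractures drop out of sensitivity.** Only those with a mark elsewhere do. Misses with no mark remain false negatives, and if w = 0 there is no distortion.
- **The AI gain is biased towards zero.** That needs AI to cut wrong-site marks by enough to outweigh the rise in c. The tool displays a box at a suspected fracture, which could reduce such marks, but it also displays indeterminate boxes, which could add some. The article gives no rates, so the direction is open.
- **Each view is scored separately, so a fracture marked on one view only is a miss on the other.** The Reference standard section says "A bounding box around the entire area of bone fracture on each image (if present) will be assigned", which leans that way. But the article uses radiograph, examination, case and image loosely for the same 500 items and never says that views are scored one by one.
- **The sex counts show that the specificity denominator is wrong.** The article says "The dataset will consist of 256 boys (97 with fractures) and 245 girls (84 with fractures", and 256 + 245 = 501 against 500 examinations. This is a clerical slip unrelated to the scoring rule, and it adds no weight here.

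**Conclusion.** The rule is wrong as written. A fractured case marked only at the wrong site is a false positive and never a false negative. With the usual denominators, sensitivity is inflated by the factor 1/(1 - w), and specificity takes in abnormal cases. Both directions follow from the rule for any w above zero.

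The size rests on assumed rates. At c = 0.80 the inflation of sensitivity is 1.6 points at w = 2%, 8.9 points at w = 10% and 14.1 points at w = 15%. With 10% false calls on normals, specificity loses 1.0, 4.8 and 7.1 points respectively.

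The distortion of the AI contrast has no fixed direction. A real gain is overstated if w stays the same or rises, and understated or even reversed if AI cuts w far enough. Because these measures carry the primary objective, the rule should be corrected before analysis.

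**What to change.** Score each examination once per reader and stage, and state the denominators.

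- **Sensitivity:** abnormal examinations with a mark inside a ground-truth box, divided by all abnormal examinations. Every other abnormal examination is a false negative, including those marked only at a wrong site.
- **Specificity:** normal examinations with no mark, divided by all normal examinations.
- **Extra marks:** report marks outside a box on abnormal examinations separately; they do not enter specificity.

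The cost is a few sentences in the analysis section. The marks are already collected, so no new data are needed. There is one small downside: with 183 fractures in 181 patients, a few examinations contain more than one fracture, and finding one would count as a full true positive. A per-fracture sensitivity reported as a supplementary result covers this.

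### A fractured image marked only at the wrong site is scored as a false positive and not as a missed fracture, so the denominators of sensitivity and specificity depend on where readers mark

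*Protocol article*

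**What the plan says.** The protocol article, under Statistical methods/data analysis plan, gives three scoring rules.

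- True positive: the reader's mark "falls within the area of the predefined ‘ground truth bounding box’ area set by the reference radiologists".
- False positive: "If the mark made by a reader falls outside a bounding box, it will be counted as a false positive". Fractured and normal images are not distinguished.
- False negative: "Where a bounding box was set by the ground truth, but no mark made on the image then a false negative result will be assigned".

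A true negative is not defined. The measures to be derived, with and without AI, are "sensitivity, specificity, positive predictive value and negative predictive value". Estimates are to come from multilevel logistic models with a random intercept for reader, and the denominators of those models are not stated. The primary objective is the change in readers' diagnostic accuracy between the two stages. The dataset has 500 examinations, "comprising 183 fractures in 181 patients".

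**The concern.** When a reader marks the wrong place on a fractured image, the fracture has been missed. Under the three rules that read is a false positive, and it does not meet the false-negative definition because a mark was made. Two things follow if the cells are used as defined. The missed fracture leaves TP+FN, so sensitivity rests only on fractured images that were hit or left blank. The same read also enters TN+FP, so specificity takes in images that are not normal.

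Both denominators then depend on reader behaviour and can differ between stages, although the same cases are read twice. The AI tool's output is itself positional: it can draw "a region of interest on the radiograph with a white square box stating presence of a fracture". The share of wrong-site marks is therefore something the intervention might change. A with-versus-without difference in sensitivity or specificity could partly reflect a moving denominator and not a change in detection. The rules also leave the unit open: a fractured image with one mark inside and one outside the box satisfies both the true-positive and the false-positive definition.

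**Working it through.** **Inputs.** From the article: 181 examinations with a fracture out of 500, hence 500 − 181 = 319 without. Not in the article, so assumed and varied: s, w and f, as shares of fractured cases correctly marked, fractured cases marked only at a wrong site, and normal cases falsely marked. Each case contributes one count per reader. The article states no figure that depends on the scoring rule, so there is none to reproduce.

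**Cells per reader under the literal rule**

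| Read | Count | Cell |
|---|---|---|
| Fractured, mark in box | 181s | TP |
| Fractured, marked only elsewhere | 181w | FP |
| Fractured, no mark | 181(1−s−w) | FN |
| Normal, marked | 319f | FP |
| Normal, no mark | 319(1−f) | TN (inferred; not defined) |

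**Formulas**

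- Literal sensitivity = TP/(TP+FN) = s/(1−w). On all fractured cases it is s.
- Literal specificity = TN/(TN+FP) = 319(1−f)/(319+181w). On normal cases only it is 1−f.

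**Effect on levels**

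- Sensitivity, s = 75%: w = 5% gives 0.75/0.95 = 78.9%; w = 10% gives 0.75/0.90 = 83.3%.
- Specificity, f = 10%: w = 5% gives 287.1/328.05 = 87.5%; w = 10% gives 287.1/337.1 = 85.2%. The value on normal cases is 90%.

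**Effect on the difference between stages.** Assume s goes from 75% to 85% and f from 10% to 8%. The true changes are +10.0 points in sensitivity and +2.0 points in specificity.

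| w without AI → with AI | Literal sensitivity | Change | Literal specificity | Change |
|---|---|---|---|---|
| 0 → 0 | 75.0% → 85.0% | +10.0 | 90.0% → 92.0% | +2.0 |
| 5% → 5% | 78.9% → 89.5% | +10.5 | 87.5% → 89.5% | +1.9 |
| 5% → 2% | 78.9% → 86.7% | +7.8 | 87.5% → 91.0% | +3.5 |
| 10% → 2% | 83.3% → 86.7% | +3.4 | 85.2% → 91.0% | +5.8 |
| 2% → 5% | 76.5% → 89.5% | +12.9 | 89.0% → 89.5% | +0.5 |

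Changes are taken from unrounded values. With equal w the sensitivity difference is only scaled by 1/(1−w): 10/0.95 = 10.5.

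**A case where all the gain is relocated marks.** Let s go from 75% to 83%, w from 10% to 2%, and f stay at 10%. Sensitivity truly rises by 8.0 points; the rule gives 0.83/0.98 − 0.75/0.90 = 84.7% − 83.3% = +1.4. Specificity is truly unchanged; the rule gives 287.1/322.62 − 287.1/337.1 = 89.0% − 85.2% = +3.8.

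**The case against.** The strongest reply is that the article never writes out the formulas for sensitivity and specificity. It says that the estimates come from logistic models, and the usual model for sensitivity is hit or no hit among all reference-positive cases, with specificity modelled among reference-normal cases. Analysed that way, a wrong-site mark is a non-hit, and neither measure is distorted. A condensed article may also leave model denominators to a fuller plan. This stands as a limit: the analysis may in practice be sound. It does not dispose of the point, because the article does not leave scoring open. It states a rule, the false-negative definition in that rule excludes wrong-site reads, and nothing elsewhere overrides it.

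It also stands that w may be small. The reference box covers the whole fracture area, and each case is a radiograph of a single joint region.

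Three stronger readings are tempting but not supported.

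- A reader might infer that AI will make wrong-site marks rarer, so that the sensitivity gain is bound to be understated. The article gives no wrong-site rate. The tool also produces dashed boxes for indeterminate findings, and nothing says that its boxes are always well placed. If w rose, the gain would be overstated.
- A reader might set these distortions against the 0.05 in Sample size and power calculation. That 0.05 is a difference in AUC between reader and AI algorithm, not a change in sensitivity or specificity between stages.
- A reader might add that a second fracture in the same child could go uncounted. The surplus is 183 − 181 = 2 fractures, about 1% of 183. The false-negative rule works per image, so an unmarked boxed image of the same child can still be a false negative.

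**Conclusion.** The concern holds as a fault in a stated rule. Followed literally, the rule keeps wrong-site reads of fractured images out of the missed fractures and puts them among the false positives, so both denominators vary with reader behaviour in the comparison that serves the primary objective. Any w above zero raises literal sensitivity above s and lowers literal specificity below 1−f.

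The effect on the difference between stages cannot be fixed from the article. Over the assumed values, a true gain of 10 points in sensitivity is reported as anything from +3.4 to +12.9, and a true gain of 2 points in specificity as +0.5 to +5.8. With no wrong-site marks there is no bias, and with equal rates in both stages the effect is slight. These figures assume one count per case and pooled body parts, and they apply only if the cells are used as defined.

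**What to change.** Replace the three rules with one that is mutually exclusive and exhaustive.

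1. State the unit of analysis, examination or image.
2. Reference-abnormal unit: TP if at least one mark lies in a reference box; otherwise FN, including when the only marks lie elsewhere.
3. Reference-normal unit: TN if the reader selects 'no fracture'; otherwise FP.
4. Model sensitivity on all reference-abnormal units and specificity on all reference-normal units, so that the denominators are the same in both stages.
5. Report wrong-site marks on abnormal units as a separate mislocalisation rate by stage.
6. State how those reads enter PPV and NPV. Predictive values condition on the reader's call, and such a unit was called positive although it counts as FN for sensitivity, so this does not follow from rules 2 and 3.

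The readers' marks are already to be collected, so the cost is rewording and a change to the scoring script. Where wrong-site marks occur, reported sensitivity will be lower than under the present rule, and reported specificity higher.
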